### 9.3 CRITERIA FOR CONTINUATION AT V2

Subjects having Visit 2 within maximally 3 days after onset of common cold symptoms according to predefined criteria for required symptoms, and, for verum group, start of IP use, will continue study participation.

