### 10.2 DOSAGE AND USE OF IP

The spray should be applied every second hour up to 6 times with each time 2 puffs (1 dose) per occasion. At V1, the subject will be instructed on the use and the application demonstrated.

[figure not shown]

Figure 2: Application of spray

Depending on the timepoint of treatment onset, there may be less IP applied on the first day of use.

The IP use should start when following conditions have been fulfilled:

- answering "Yes" to either of the questions in the subject diary: "Do you think/feel you have a cold?" or "Do you think/feel you are coming down with a cold (might be having first signs of cold)?"
- Jackson score of at least 1 (mild = sensible, but not disturbing or irritating) for any symptom except headache

The IP should be used until 2 days after the subject is symptom free (=answering "No" to the question "Do you think that you are still sick with this respiratory infection?" for 2 days in a row), but not longer than 12 days in total.

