## **10.6 BLINDING**

In this single-blind study, the subjects, the study site staff handling the IP and the study monitors will not be blinded to treatment assignment. The investigator performing the cold symptom assessment at V2, the project manager, the statistician and all further study team members will be blinded to treatment assignment.

The unblinded site study staff and the monitor(s) will take utmost care not to unblind the investigator performing the cold symptom assessment at V2 or any further blinded study team members at any occasion during the entire study duration.

The subjects will be instructed not to unblind the investigator.

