### 14.1.3 Statistical methods

All end points as well as the concurrent and safety variables will receive an explorative examination and will be descriptively assessed. For the metric data (continuous data) the statistical characteristics will be given (number, mean, standard deviation, median, extremes, quartiles). For ordinal data (discrete data) number, median, interquartile range and extremes will be calculated. If found suitable, ordinal data will be considered as supplementary metric data. For all nominal data the frequency distribution will be presented in frequency tables. The values of metric data can be merged in ordinal classes according to clinical criteria to determine their frequency distribution. Explorative estimation for the structural consistency of the groups regarded will be proved by a descriptive comparison of demographic data, values at screening and secondary (further) endpoints.

In case of generated statistical hypotheses from the above defined descriptive analyses, the subsequent exploratory statistical tests are as follows (for reasons of small samples and/or potentially non-normal distributions):

- Mann-Whitney-U test for comparison independent groups,
- Paired Wilcoxon test for the pre-post comparison within groups,
- Chi-Square test for the comparison of frequencies for independent groups.

All p-values from statistical tests are to be understood as exploratively. That means, the results may deliver interesting insights in the underlying object of research, but those findings don't qualify for a confirmative generalization. Because of the exploratory character of the study no adjustment for multiple testing will be accomplished.

The FAS population will consist of all randomized subjects for which at least one data point after onset of cold symptoms is available, and, for verum group only, who received at least one dose of IP upon onset of cold symptoms. The VCAS population will consist of subjects from FAS without any major violations of the CIP. The assignment to the study populations will be performed before unblinding and start of analysis.

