### **16.3 CIP DEVIATIONS**

No systematic or prospective deviations from the CIP are tolerated. CIP deviations will be evaluated during blind data review by the sponsor, the CRO, and the biometrician in order to define the study data sets.

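### The full analysis set requires a dose of IP in the verum arm only: a one-sided filter after randomisation that also conflicts with assigning the sets before unblinding

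*Protocol*

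**What the plan says.** **Analysis sets.** Protocol section 14.1.3 gives one condition for both arms, "all randomized subjects for which at least one data point after onset of cold symptoms is available", and adds a second for one arm: "and, for verum group only, who received at least one dose of IP upon onset of cold symptoms". The second set is built on the first: "The VCAS population will consist of subjects from FAS without any major violations of the CIP". On timing: "The assignment to the study populations will be performed before unblinding and start of analysis".

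**Who assigns, and who is blinded.** Section 16.3 sets out how the data sets are defined: "CIP deviations will be evaluated during blind data review by the sponsor, the CRO, and the biometrician". Section 10.6 leaves subjects, the staff who handle IP and the monitors unblinded. It blinds the investigator who assesses the cold at V2, and adds that "the project manager, the statistician and all further study team members will be blinded to treatment assignment". Section 10.5 keeps the randomisation list locked until database closure. In section 12.7.1 the diary field for IP use exists for verum subjects only.

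**Onset.** The synopsis (visit schedule) applies the onset criteria to both study groups and refers to its entry on duration of intervention. That entry and section 10.2 give the detail: a yes to one of the two cold questions, plus a "Jackson score of at least 1 (mild = sensible, but not disturbing or irritating) for any symptom except headache".

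**Continuation.** Section 9.3 ties continuation to a V2 within 3 days of onset "and, for verum group, start of IP use, will continue study participation".

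**The concern.** Whether a verum subject takes a first dose is decided after randomisation, by someone who knows the assignment. Making FAS membership depend on it in one arm means that the two arms are no longer selected by the same rule. No corresponding control can be removed, because controls have nothing to take.

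The stated goal (section 14.1.1) is to judge several assessments by the size of the treatment effects observed, so a distortion of those effects touches the purpose of the study. The main endpoint that counts subjects whose initial signs did not become a cold is the most exposed. A verum subject whose signs faded before the first spray would be a prevented case but leaves the denominator. A control with the same course stays and counts as prevented.

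A rule that applies to one arm also cannot be applied without knowing the arm, yet the people named to define the sets are meant to be blinded when they do so.

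**Working it through.** **1. The plan's own figures.** There is no calculation to reproduce. Section 14.1.5 says that no statistical planning of sample size is possible and sets 200 on practical grounds. With 1:1 allocation (section 10.5) that is 200 / 2 = 100 per arm.

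**2. The rule applied to four subjects, each with onset and a later data point.**

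| Arm | Dose taken | In FAS |
|---|---|---|
| Verum | yes | yes |
| Verum | no | no |
| Control | none to take | yes |
| Control who would not have dosed had they been given IP | none to take | yes |

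Rows 2 and 4 are the same kind of subject and are treated differently. The VCAS is a subset of the FAS, so it cannot restore row 2.

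**3. Continuous scores.** Let f be the share of verum subjects with onset who take no dose, and D the difference in mean between undosed and dosed, in SD. The whole verum arm has mean (dosed mean) + f × D, so dropping the undosed shifts the verum mean by f × D in absolute size. The protocol gives neither f nor D; both are assumptions.

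- f = 0, or D = 0: shift 0
- f = 1%, D = 0.5: 0.005 SD
- f = 5%, D = 0.5: 0.025 SD
- f = 15%, D = 1: 0.15 SD

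The standard error of an arm difference at 100 per arm is √(1/100 + 1/100) = 0.141 SD. The range is therefore 0 to 0.15 / 0.141 = 1.06 standard errors.

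**4. Prevention percentage.** Suppose there is no treatment effect. Let p be the true prevention rate in both arms, u the undosed share of verum, and q the prevention rate among the undosed. The verum rate in the FAS is (p − u × q) / (1 − u). All three inputs are assumptions. With p = 0.30 and u = 0.10:

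- q = 0.8 (the undosed mostly had aborted colds): (0.30 − 0.08) / 0.90 = 24.4%, a shift of −5.6 points
- q = 0.30 (the undosed resemble the rest): 30.0%, no shift
- q = 0: 0.30 / 0.90 = 33.3%, a shift of +3.3 points

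Over p = 0.2 to 0.4 and u = 2 to 15%, the shift runs from −0.8 to −10.6 points for q = 0.8 and from +0.4 to +7.1 points for q = 0. It goes to 0 as u goes to 0. The sign depends on who skips the spray, which the protocol cannot tell us.

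**5. Blinding.** A reviewer without the list sees two kinds of record. One has IP use entered, which identifies a verum subject. The other has none, and belongs either to a control (keep) or to an undosed verum subject (remove). The second kind cannot be sorted without the arm. Sections 10.5, 10.6 and 16.3 give the reviewers no arm information at that point.

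**The case against.** **The bias may be negligible.** Verum subjects receive the spray and instructions at V1, agreed on entry to use it, and need only one dose to qualify. The undosed share could be close to zero, and undosed subjects need not differ from the others. This stands, and it is why the range starts at 0.

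**The study is exploratory.** No hypothesis is pre-specified and no error rate is controlled. This also stands: the harm is to effect estimates and not to a confirmatory test.

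**The blind review could be made to work.** Unblinded site staff or monitors could pass on a dosing flag. That is possible, so it would go too far to say that the sets can never be assigned blind. The protocol gives nobody this task, however, and a flag that can only be set for verum subjects still tells its recipient the arm of everyone flagged.

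**Stronger readings that the protocol does not support.**

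- A reader might infer that a control with headache alone enters the FAS while a verum subject with headache alone does not. The synopsis applies the onset criteria to both groups and points to the entry that excludes headache, so onset in 14.1.3 can be read as the same event in each arm.
- A reader might infer that section 9.3 ends participation for undosed verum subjects. The synopsis counts the V2 window from the first yes and first symptom as well as from first IP use, and the flow chart heads V2 by days after the start of IP use. The phrase can therefore be a timing anchor. It is ambiguous, and should be clarified for that reason only.
- A reader might take the FAS to be the only efficacy set. There is also the VCAS, although it inherits the rule.

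**Conclusion.** The concern holds in a limited form. Section 14.1.3 fixes a dose condition in one arm of a trial in which subjects are unblinded, and both defined sets carry it. This can bias the observed treatment effects, including the prevention percentage, in an unknown direction. Under assumed undosed shares of 0 to 15% and differences of 0.5 to 1 SD between undosed and dosed, the bias in a continuous score is 0 to 0.15 SD, at most about one standard error at 100 per arm. It is exactly zero if nobody skips the spray or if those who do resemble the rest.

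Separately, the condition as written conflicts with the promise of assignment before unblinding and with the blind data review. Neither part is a matter left open for the SAP: the protocol states the rule and the promise side by side.

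One limit remains in any case. Onset is reported by subjects who know their arm, and an equal FAS rule does not remove that.

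**What to change.** 1. **FAS.** Define it identically in both arms: all randomised subjects who meet the onset criteria that the synopsis already applies to both groups and who have at least one later data point, analysed as randomised whether or not IP was used. Any shift caused by the dose condition is then 0, whatever the undosed share.
2. **Dosing.** Use IP use only for the VCAS or a secondary set.
3. **Order of sign-off.** Sign off the FAS from an extract without verum-only fields (IP use, accountability, device deficiencies, global ratings of the IP). For the VCAS, either have an unblinded person outside the analysis team supply the dosing flag, or state that this set is not assigned blind. Withholding the fields for the VCAS as well would leave its dosing rule impossible to apply.
4. **Section 9.3 and synopsis.** Clarify that the start of IP use is a timing anchor for V2, so that data from undosed verum subjects are still collected.

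Section 14.1.6 already allows the SAP to record deviations from the protocol's analyses before database closure, so the changes to the sets can be entered there if the protocol is not amended. The cost is wording and, if any undosed verum subjects enter the FAS, a slight dilution of the observed effect.

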### 14.1.4 Drop-outs

There will be no replacement of drop-outs after V2.

#### **14.1.5 Sample size estimation**

At the current stage of knowledge, no reliable information about the underlying scientific object of research (assessments of common cold symptoms) is available. Therefore, no statistical planning of sample size is possible and the number of 200 subjects is only determined by practical needs of the investigator, taking account for the inter- and intra-individual variability and underlying physiological processes.

The proposed sample size is expectedly required to collect plausible data with respect to the main study goal, the evaluation of various assessments of common cold symptoms for proof of efficacy of CMS016317.

Comparable sample size numbers have been previously reported in common cold studies with natural products (e.g. Auinger et al, 2013; Riede et al, 2013), though these studies were not focussing on the assessment evaluation.

Given the favourable risk-to-benefit-ratio of CMS016317 (see section 6), the study subjects may not be considered as exposed to any substantial risks due to study participation.

#### **14.1.6 Statistical analysis plan/report**

Before database closure, a statistical analysis plan (SAP) will be provided, presenting planned statistical analyses as well as any possible deviations or additions of the data analyses originally defined in the CIP before clinical study start. Changes in the planned statistical methods and analyses after approval of the SAP will be documented in the clinical study report. The results of the statistical analyses of the study will be documented in the statistical report. The statistical report will provide the basis for the preparation of the study report.

## **15 ETHICAL AND LEGAL CONSIDERATIONS**

### **15.1 REGULATORY ASPECTS**

This clinical investigation will be performed based on the principles of the World Medical Association (Declaration of Helsinki, version applicable for the involved investigators), ICH GCP E6, German Act on Medical Devices (MPG) §23b and ISO 14155. Further, for reporting of deficiencies, MEDDEV 2.7/3 revision 3 and for reporting of incidents, the Ordinance on Medical Devices Vigilance and MEDDEV 2 12-1 rev. 8 Vigilance will be followed.

### **15.2 INDEPENDENT ETHICS COMMITTEE**

This clinical investigation will be evaluated by an EC before inclusion of the first subject. The CRO will submit the CIP and relevant study documents to the EC to request for opinion.

### **15.3 SUBJECT INFORMATION AND INFORMED CONSENT FORM**

The subject must declare informed consent before participation in the clinical investigation, i.e. before any study specific procedure is performed.

The investigator will ensure that the subject is given full and adequate oral and written information (subject information) about the nature, purpose, consequences and possible risk of the clinical investigation. Subjects must be informed that they are free to withdraw from the study at any time without any resulting disadvantages, how personal and health-related data will be collected and used during the study, and that their identity and medical information will not be disclosed. The subject should be given the opportunity to ask questions and should be allowed sufficient time to consider the information provided. The subject's signed and dated informed consent must be obtained before conducting any study specific procedure. The investigator(s) must store the original, signed and dated informed consent forms in the ISF. A copy of the signed and dated informed consent form must be given to the subject, along with a copy of the insurance conditions.

If new information becomes available that can significantly affect a subject's future health and medical care, that information will be provided to the subject(s) affected in written form. If relevant, all affected subjects will be asked to confirm their continuing informed consent in writing.

### **15.4 INVESTIGATOR'S OBLIGATIONS**

By signing the CIP, the investigator confirms to adhere to the CIP and all applicable national and international regulations and guidelines. The investigator has to ensure that all other study (sub-) investigators and study personnel assisting in the present clinical investigation are qualified by training for their individual responsibilities and functions and informed about the clinical study documents, about the IP, and the investigational procedures.

A delegation log will be set up and updated during the course of the study, in which the investigator will list all study team members including their delegated responsibilities.

The investigators will permit access to source data for study-related monitoring as well as in case of audits and inspections.

### **15.5 AMENDMENTS TO THE CIP**

All amendments to the CIP need agreement between the sponsor and the principal investigator. Every substantial amendment to the CIP or the subject information including the informed consent form needs to be reviewed by the EC prior to implementation. Preparation and submission of any amendments will be performed by the CRO.

Under emergency circumstances, deviations from the CIP to protect the rights, safety and well-being of human subjects may proceed without prior approval of the sponsor and the EC.

## **15.6 DATA PROTECTION AND CONFIDENTIALITY**

The CRO and the study sponsor's representative will ensure the right of the study participants to protection from invasion of privacy. The investigators have to comply with the data protection laws of the Federal Republic of Germany ("Bundesdatenschutzgesetz").

Following consent to participation in the clinical investigation, the subject will be assigned a screening number. Subjects meeting the eligibility criteria will be assigned a random number. The collected data will be made available to the CRO and the study's sponsor only in pseudonymous form, to minimize the chances of matching the data to an individual person. Only the age and gender will be recorded in CRF (no initials, no date of birth). The paper based identification list will be confidentially retained by the investigator.

In case of SAE related documentation provided to the CRO and the study sponsor, the investigator will ensure the pseudonymity of the copies of the documentation provided.

With the receipt of the CIP, the investigator is bound to treat all information contained herein as strictly confidential. He/she is further required to inform his support staff or other personnel that may have access to the CIP of this confidentiality.

## **16 QUALITY CONTROL AND QUALITY ASSURANCE**

Quality assurance and quality control systems will comprise e.g.:

- Training
- Monitoring visits
- Double data entry
- SOPs of the CRO

### **16.1 TRAINING**

The investigator and monitor must make sure that study staff has been appropriately trained and has received the relevant information relating to this study.

### **16.2 MONITORING**

The purpose of monitoring is to verify that the conduct of the clinical investigation complies with the approved CIP, subsequent amendments and applicable regulations. Before the initiation of the clinical investigation, a monitor will verify the adequacy of the investigational site and facilities and discuss with the investigator(s) and other personnel involved in the clinical investigation their responsibilities with regard to the clinical investigation. At the end of the clinical investigation a close-out visit will be performed at the investigational site.

During the clinical investigation, a monitor will have regular contacts with the investigational site, including visits to verify that all data in the CRFs are complete, recorded in a timely manner and consistent with source data, that signed and dated informed consent forms have been obtained from each subject at the time of enrollment and before any clinical study-related procedures are undertaken, that the clinical investigation is being performed according to the CIP, and in accordance with ICH GCP (E6) and applicable regulations.

Further details with respect to monitoring including the extent of source data verification will be laid out in a Monitoring Plan.

### **16.3 CIP DEVIATIONS**

No systematic or prospective deviations from the CIP are tolerated. CIP deviations will be evaluated during blind data review by the sponsor, the CRO, and the biometrician in order to define the study data sets.

### **16.4 AUDITS AND INSPECTIONS**

Authorised representatives of the sponsor and / or regulatory authorities, if applicable, may visit the study centres to perform audits or inspections, including source data verification. The purpose of an audit or inspection is to systematically and independently examine all intervention-related activities and documents to determine whether these activities were conducted, and whether data were recorded, analysed and accurately reported according to the CIP, ICH GCP, ISO 14155 and applicable regulations.

## **17 DATA HANDLING AND RECORD KEEPING**

### **17.1 SOURCE DATA**

All required source data will be recorded in the subject file and subsequently transcribed into CRF. The source data entries must allow to assess whether the study including all procedures was conducted according to CIP. The study diaries and questionnaires act both as source data as well as a part of the CRF.

### **17.2 DATA DOCUMENTATION**

The CRO will provide the investigator with a CRF for each subject. In this CRF, the investigator (or delegate) will in a pseudonymised manner enter all ascertained findings concerning the subject which are documented in the source data. Only the screening and randomization numbers will designate the subject in the CRF.

It is the investigator's responsibility to maintain adequate and accurate CRF to record all observations and other data pertinent to the study. The CRF must be completed with a ballpoint pen, in a correct and legible manner and must be kept current at all times. In no case may corrections be erased or concealed. If a correction should be necessary, the incorrect entry is to be left with a single strike through. The correction is to include the date and signature of the authorized person making the correction.

The investigator confirms by signature the accuracy of all entries in the CRF. The CRF will be checked by the monitor according to the monitoring plan. The investigator should keep subject records separate from the CRF at the investigational site.

